## Abstract

**Background:**

Depression is one of the most common reasons for consulting a General Practitioner (GP) within the UK. Whilst antidepressants have been shown to be clinically effective, many patients and healthcare professionals would like to access other forms of treatment as an alternative or adjunct to drug therapy for depression. A recent systematic review presented some evidence that physical activity could offer one such option, although further investigation is needed to test its effectiveness within the context of the National Health Service.

The aim of this paper is to describe the protocol for a randomised, controlled trial (RCT) designed to evaluate an intervention developed to increase physical activity as a treatment for depression within primary care.

**Methods/design:**

The TREAD study is a pragmatic, multi-centre, two-arm RCT which targets patients presenting with a new episode of depression. Patients were approached if they were aged 18-69, had recently consulted their GP for depression and, where appropriate, had been taking antidepressants for less than one month. Only those patients with a confirmed diagnosis of a depressive episode as assessed by the Clinical Interview Schedule-Revised (CIS-R), a Beck Depression Inventory (BDI) score of at least 14 and informed written consent were included in the study. Eligible patients were individually randomised to one of two treatment groups; usual GP care or usual GP care plus facilitated physical activity. The primary outcome of the trial is clinical symptoms of depression assessed using the BDI four months after randomisation. A number of secondary outcomes are also measured at the 4-, 8- and 12-month follow-up points including quality of life, attitude to and involvement in physical activity and antidepressant use/adherence. Outcomes will be analysed on an intention-to-treat (ITT) basis and will use linear and logistic regression models to compare treatments.

**Discussion:**

The results of the trial will provide information about the effectiveness of physical activity as a treatment for depression. Given the current prevalence of depression and its associated economic burden, it is hoped that TREAD will provide a timely contribution to the evidence on treatment options for patients, clinicians and policy-makers.

Trial registration: ISRCTN 16900744

## Background

Depression is a leading contributor to disability in the UK and is associated with a decrement of health greater than many other chronic diseases [1,2]. It impacts not only upon the life of the individual but also upon their carers, employers and society as a whole [3-5]. Whilst antidepressants are the most commonly prescribed treatment for depression, there is concern about their use and effectiveness, especially in mild/moderate cases [6-8]. Cognitive behavioural therapy and counselling are alternatives or adjuncts to medication, but access to therapists within United Kingdom (UK) primary care is variable and can involve long waiting times. For these reasons, there is a need to identify other effective non-pharmacological interventions for the management of depression.

A recent systematic review presented some evidence that physical activity could be an effective treatment for depression, although much of the research considered had important limitations [9].

Many randomised controlled trials (RCTs) conducted to date have recruited from a non-clinical setting or have offered financial or other incentives to participate [9,10]. Results from such trials are difficult to generalise to patients who present routinely to primary care since community volunteers or paid subjects are likely to display higher levels of motivation than potential participants who are identified within the clinical setting.

Reported trials have frequently been small and of poor quality. Many have used inadequately concealed randomisation procedures or failed to conduct proper intention-to-treat (ITT) analyses, so may have exaggerated any observed treatment effects [9,11]. Studies have also generally been insufficiently powered to detect a meaningful difference between the treatment groups, with even the largest study reporting fewer than 50 participants per treatment arm [12].

Length of follow-up has been problematic, with those studies of shortest duration often reporting the largest effects, suggesting that any impact may be diminished or disappear altogether in the longer term. Indeed, only a small proportion of RCTs have investigated whether any benefits outlasted the duration of the intervention itself [13].

Little is known about the type, intensity or duration of physical activity that might prove effective for the treatment of depression. The context within which any intervention is delivered may also be pivotal in terms of the uptake and sustainability of physical activity for the individual. Furthermore, any intervention will need to consider the feasibility and practicality of delivery, as well as addressing any issues of motivation, energy and self-esteem prevalent within a depressed population.

### Aim

The aim of this paper is to describe the protocol for an RCT designed to evaluate an intervention developed to increase physical activity, as a treatment for depression within primary care.

## Methods/design

### Recruitment of participants and baseline assessment

The TREAD study is a pragmatic, multi-centre, two-arm RCT into which patients recently diagnosed with a new episode of depression are recruited from primary care (as shown in Figure 1). Recruitment for the trial took place over a 27-month period between August 2007 and October 2009 in general practices from the Bristol and Exeter areas. Patients could be included if they were aged 18-69, had recently consulted their GP for depression and had either recently started taking antidepressants (within four weeks of their baseline assessment and following an antidepressant free period of at least one month) or were not currently on antidepressants. Ethical approval for the study was given by West Midlands Multi-centre Research Ethics Committee (MREC) and research governance approval was obtained from the relevant local Primary Care Trusts (PCTs).

**Figure 1 F1:**
[figure not shown]
**A flowchart of the TREAD trial design**.

Individuals who were unable to complete self-administered questionnaires in English, or had medical contraindications to physical activity, psychosis, bipolar disorder or any serious substance abuse problem were excluded from the study. Women pregnant at the time of recruitment were also automatically excluded but those women who became pregnant in the course of their study participation were encouraged to continue under their GP's supervision.

The majority of patients referred to TREAD were identified during routine consultations, when they were given a patient information leaflet by their GP and, if interested, asked to provide written authority to enable further contact by the research team. In some practices, computer systems were also regularly searched for details of patients recently diagnosed as depressed or prescribed an antidepressant, in an effort to alert GPs to potentially eligible individuals. In this instance, patients were sent information about the study from their surgery and encouraged to respond to the research team directly, if interested, using a reply-paid slip. Once a referral was received, a researcher telephoned the patient to introduce the study formally, make initial eligibility checks and to arrange an appointment for baseline assessment. Referred patients were visited at home or at their GP surgery in order to obtain consent and assess eligibility using the Clinical Interview Schedule (CIS-R) [14] and the Beck Depression Inventory (BDI) [15]. Only patients with a confirmed diagnosis of a depressive episode according to the International Statistical Classification of Diseases and Related Health Problems 10th Revision (ICD-10), a BDI score of at least 14 and informed written consent were included in the study.

In addition to the RCT, a nested qualitative study will investigate the experience and acceptability of the intervention for both participants and health professionals. An economic analysis will also be performed using a quality of life measure and information gathered on health service use to assess the cost effectiveness of the intervention.

### Randomisation procedure

Eligible and consenting patients were individually randomised at the end of their baseline assessment to one of two treatment groups; usual GP care or usual GP care plus facilitated physical activity. Randomisation was stratified to take account of antidepressant use (yes, no) and minimised by severity of depression (CIS-R score of ≤25, 26-33, >34 at baseline), recruiting centre (Bristol, Exeter) and level of physical activity (≤1, 2-3, >4 days per week where at least 30 minutes of moderate intensity physical activity was being undertaken). Allocation was concealed from the researcher using an automated telephone randomisation system which was administered remotely and used a computer-generated code.

### Follow-up

Follow-up data collection is scheduled at three time-points; 4, 8 and 12 months post-randomisation. The 4-month follow-up was chosen as the primary outcome time point since it represents the stage in the intervention period at which we expect to observe the largest effect. The 8-month follow-up coincides with the end of the intervention delivery, whilst the 12-month follow-up will enable the investigation of any longer term effects of the intervention on study outcomes. All follow-up data collection employs a self-report research instrument.

In order to maximise retention, researchers meet study participants to supervise the data collection process at the 4 and 12-month follow-up points wherever possible. Due to restricted resources, 8-month follow-up is conducted solely using a postal questionnaire. Any participants unable to attend their 4 and 12-month follow-up sessions are contacted by telephone to arrange a further appointment or sent the questionnaire by post if re-arranging a face-to-face session is difficult.

### Intervention

All study participants are encouraged to follow the advice of their GP regarding depression and its treatment throughout their involvement in the trial. In addition to this, participants in the intervention arm of the study are offered the support of a Physical Activity Facilitator (PAF) over an 8-month period. All PAFs are trained specifically for the study and receive regular supervision and feedback to maximise fidelity to model.

The TREAD intervention is theoretically-driven [16,17] and tailored to address the specific challenges of isolation, apathy and social anxiety which are common within a depressed population. It aims to provide relatively intensive, individually tailored support in a context that will encourage maximum engagement in physical activity. Following a specially developed manual, PAFs use a range of motivational interviewing techniques and goal-setting strategies to encourage participants' uptake of a range of acceptable and locally available physical activities. The rationale and development of the TREAD intervention is discussed in more detail in Haase et al [18].

The intervention comprises an initial hour-long, face-to-face assessment session followed by a series of up to ten short telephone contacts and two further half-hour, face-to-face meetings, with the scheduling left to the discretion of the PAF and the participant. The expectation is that at least five sessions including one face-to-face meeting would be delivered by the primary outcome point i.e. by 4-month follow-up.

### Outcome measures

#### Primary outcome

The Beck Depression Inventory (BDI) [15] is collected by self-report measure at the 4-month follow-up point [15]. The resulting score is treated as both a continuous (range 0 to 63) and binary (where less than 10 indicates recovery) variable in order to provide a quantitative measure of improvement and an estimate of the proportion of patients reaching symptomatic recovery.

#### Secondary outcomes

The longer term effects of the intervention are measured using the BDI at the 8 and 12-month follow-up points and the Short Form-12 Health Survey (SF-12) [19] at 4, 8 and 12-month follow-up points. Attitude to, and involvement in physical activity are also measured by self-report at the same three follow-up points. Antidepressant use is assessed using a self-reported measure of medication adherence at all three follow-up points whilst GPs' records will provide details of antidepressant prescription over the entire 12-month follow-up period.

### Statistical Analysis

The analysis and reporting of this trial will be undertaken in accordance with Consolidated Standards of Reporting Trials (CONSORT) guidelines [20] with the primary comparative analyses conducted on an intention-to-treat (ITT) basis using linear and logistic regression models without imputation of missing outcome data. Descriptive statistics of key clinical and socio-demographic variables will be obtained as a means of detecting any marked imbalance between the randomised groups at baseline, with investigation of the effects on the primary analyses of additional adjustment for any such variables.

The primary outcome measure (BDI score at 4-month follow-up point) will be used and presented in both binary and a continuous form, adjusting for BDI score at baseline and the stratification/minimisation variables. For the continuous outcome, the result will be presented as the (adjusted) difference in mean score between the intervention and control groups. For the binary outcome, the result will be presented as an (adjusted) odds ratio of recovery in the intervention group compared with the control group. Full attention will be paid to 95% confidence intervals as well as p-values.

The BDI score will also be considered in both binary and continuous form in secondary analyses, using data from the 4, 8 and 12-month follow-up points in a repeated measures analyses. These will investigate whether any between-group differences alter over time, and in the absence of any time effect, will yield an average effect over the three follow-up assessments. SF-12 sub-scores, attitude to physical activity, physical activity level and self-reported antidepressant use will be analysed employing appropriate regression techniques at 4-month follow-up and also in a repeated measures analysis conducted using 4, 8 and 12-month follow-up data. Antidepressant prescription data will be analysed as a continuous variable using all data available in an appropriate regression model. Consideration will be given to the adjustment of p-values for multiple testing.

The effect of missing data will be investigated by generating a complete dataset using the Multiple Imputation Chain Equation (MICE) method [21]. Complier-Average Causal Effect (CACE) estimates [22], or treatment efficiency, will be estimated using instrumental variable regression and will compare outcomes for those participants receiving an adequate 'dose' of the intervention with a comparable group of would-be compliers in the control arm. The extent and impact on the results of clustering by general practice will also be investigated.

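### Averaging the BDI effect over 4, 8 and 12 months when no change over time is found does not estimate the 12-month effect, which should be reported in its own right

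*Protocol article*

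**What the plan says.** The 4-month comparison is primary and is presented in any case (Statistical Analysis): "The primary outcome measure (BDI score at 4-month follow-up point) will be used and presented in both binary and a continuous form".

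The repeated-measures work on all three visits is secondary: "The BDI score will also be considered in both binary and continuous form in secondary analyses". Its reporting rule follows: "These will investigate whether any between-group differences alter over time, and in the absence of any time effect, will yield an average effect". The sentence goes on to make clear that the average is taken over all three follow-up visits.

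Three other places bear on this rule:
- Follow-up justifies the choice of 4 months because it "represents the stage in the intervention period at which we expect to observe the largest effect". It also says that the "12-month follow-up will enable the investigation of any longer term effects of the intervention on study outcomes"; the 8-month visit coincides with the end of intervention delivery.
- Secondary outcomes names BDI at 8 and 12 months as the measure of longer-term effect.
- Background, on the earlier trials, notes that the shortest studies often showed the largest effects, "suggesting that any impact may be diminished or disappear altogether in the longer term".

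**The concern.** The rule depends on the data: look for a change in the between-group difference and, if none is found, pool the visits. Pooling is a sensible summary if the effect is constant. Constancy is not what this protocol expects, because it chose 4 months as the point of largest effect.

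A non-significant interaction is weak evidence of constancy in a trial sized for a main effect at one visit. If real waning is missed, the BDI estimate that the section describes beyond 4 months is an average that includes the visit where the effect is expected to be greatest. At stake is the secondary question of whether benefit lasts after the 8-month intervention ends. A reader given only the average could take it as the answer for 12 months.

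**Working it through.** **Inputs from the protocol** (Sample size justification, Table 1, Discussion): 360 randomised, 180 per arm; 15% attrition, so 360 × 0.85 = 306 analysed, 153 per arm; SD 9; target difference 3 points; two-sided 5%.

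**Assumptions, not in the protocol:** 153 per arm at every visit; SD 9 at every visit; the same correlation ρ between any two visits, from 0.3 to 0.7; a Wald test of group by time on 2 degrees of freedom at 5%; and two patterns of true effect at 4, 8 and 12 months, namely 3, 2, 1 (partial waning) and 3, 1.5, 0 (complete waning).

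**Step 1: the plan's own figure.** The variance of a difference at one visit is v = 2 × 81 / 153 = 1.0588, so SE = 1.029. Power for 3 points is Φ(3/1.029 − 1.96) = 83.0%. Table 1 gives 82%, so the inputs reproduce it closely.

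**Step 2: power to detect waning.** Under exchangeable correlation the noncentrality is λ = Σ(dᵢ − d̄)² / [v(1 − ρ)].
- For 3, 2, 1: d̄ = 2 and the sum is 1 + 0 + 1 = 2.
- For 3, 1.5, 0: d̄ = 1.5 and the sum is 2.25 + 0 + 2.25 = 4.5.

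| True effects | ρ | λ | Detected | Missed | Average | 12-month effect |
|---|---|---|---|---|---|---|
| 3, 2, 1 | 0.3 | 2.70 | 29.3% | 70.7% | 2 | 1 |
| 3, 2, 1 | 0.5 | 3.78 | 39.5% | 60.5% | 2 | 1 |
| 3, 2, 1 | 0.7 | 6.30 | 60.6% | 39.4% | 2 | 1 |
| 3, 1.5, 0 | 0.3 | 6.07 | 58.9% | 41.1% | 1.5 | 0 |
| 3, 1.5, 0 | 0.5 | 8.50 | 74.5% | 25.5% | 1.5 | 0 |
| 3, 1.5, 0 | 0.7 | 14.17 | 93.1% | 6.9% | 1.5 | 0 |

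Simulation with 400,000 draws at ρ of 0.5 and 0.7 agrees: missed in 60.6% and 39.4% for partial waning, and 25.6% and 6.9% for complete waning. Among the misses, the mean of the average was about 2.0 and 1.5. A 1-df test of 4 against 12 months does better: 38%, 49%, 71% for partial and 69%, 83%, 96% for complete waning at ρ = 0.3, 0.5, 0.7.

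**Step 3: binary recovery.** Take an odds ratio of 1.97 at 4 months (Table 1) and, as an assumption, 20% control recovery at every visit. Waning by thirds on the log scale is detected on 2 df in 22%, 30%, 47% of trials at ρ = 0.3, 0.5, 0.7. Waning to no effect is detected in 44%, 59%, 82%.

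**Step 4: what the average estimates.** Its SE is √[v(1 + 2ρ)/3]: 0.75 at ρ = 0.3, 0.84 at 0.5, 0.92 at 0.7. For 3, 2, 1 it lies 1 point from the 12-month effect. Its 95% CI covers that effect with probability Φ(1.96 − 1/SE) − Φ(−1.96 − 1/SE), which is 76%, 78%, 79% at ρ = 0.4, 0.5, 0.6. These values are the same with or without the pre-test, because under this model the average is independent of the interaction contrasts. The shortfall shows that the average is a different estimand from the 12-month effect. It does not show that the pre-test spoils the interval.

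**The case against.** Much of the case on the other side stands.

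- **Availability of visit-specific estimates.** A reader might infer that the average will be the only later estimate, or that non-significance will be treated as proof of constancy. The article says neither. It does not say that 8- and 12-month estimates will be withheld or that lasting benefit will be claimed from the average. How absence of change is judged, and which contrasts are tabulated, may be set in a fuller document; that silence is not held against the plan.
- **Low power.** A reader might conclude that the check would usually fail. That cannot be derived from the article, which gives neither the correlation nor the amount of waning. It holds for partial waning over much of the range. It does not hold for complete waning of the continuous score at a correlation of about 0.5 or more.
- **Validity of the interval.** A reader might say that the pre-test makes the interval too narrow. Step 4 shows otherwise. For the three-visit average, which is what it is labelled to estimate, the interval has its nominal 95% coverage in this model even after a non-significant test.
- **Wording.** Read alone, the term for the time effect could suggest the general fall in BDI in both arms. The clause just before it asks whether between-group differences change, which is the group-by-time interaction, so there is no error of terminology.
- **Reach.** The primary 4-month result is always presented, so understating the 4-month effect in the average has no practical effect on it. The condition is stated for BDI alone, not for SF-12, activity or antidepressant use.

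What survives is that the pooling rule is stated in the text. A test level added elsewhere would not make absence of a detected change into evidence of constancy, or turn the average into a 12-month estimate.

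**Conclusion.** The point holds as a modest one about a secondary analysis. The stated rule pools the three visits when no change is found, although the protocol expects the effect to peak at the first of them and asks its longer-term question at the other two.

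Under the assumptions above, partial waning (3, 2, 1) would go undetected in about 39 to 71% of trials and complete waning (3, 1.5, 0) in about 7 to 41%. The average would then exceed the 12-month effect by about 1 and 1.5 points respectively. These ranges rest on the assumed test, correlation and waning patterns. The mismatch between the average and the 12-month effect needs only that the effect wanes, and it is there with or without a pre-test. The sample size and the primary conclusion are untouched.

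**What to change.** For BDI, continuous and binary, remove the condition. From the repeated-measures model with group-by-time terms, report whatever the interaction shows:
- the adjusted differences, or odds ratios, at 4, 8 and 12 months with 95% CIs;
- the group-by-time interaction;
- the three-visit average, only as a labelled summary.

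Base any statement about lasting benefit on the 12-month contrast.

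The change is one of wording, with the same data and no new sample size. The price is precision: on the continuous score a visit-specific SE is about 1.03, against 0.75 to 0.92 for the average at correlations of 0.3 to 0.7. That wider interval is the precision the trial has for the 12-month question.

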### Sample size justification

The sample size calculation was based on the BDI score as both a binary and a continuous outcome measure. As it was initially thought that 10% of the population would not be taking antidepressants at the time of recruitment, the intention was to omit these individuals from the primary analysis. The original calculation had estimated that 60% of participants in the usual care group and 73% in the intervention group would have recovered by the 4-month follow-up, that is scoring < 10 on the BDI. A difference of 13% in the proportion 'recovered', equivalent to an odds ratio of 1.8, is consistent with the lower end of treatment effects observed with antidepressant medication and is considered clinically worthwhile. With 90% power and 5% two-sided alpha, 291 recruited patients would be required for each treatment group. Previous studies using the BDI as a continuous outcome have estimated a standard deviation of about 9 points [23] and have suggested a worthwhile and feasible target difference of 3-4 points. Thus, allowing for a maximum attrition rate of 15%, the required sample size was initially calculated to be 762.

However, in the early stages of the trial, the percentage of participants not on antidepressant treatment was found to be almost 50%. Given the implications for total sample size, and that allocation was stratified by antidepressant use, it was proposed that all randomised participants should be included in the primary analysis. In addition, whilst the recovery rate of the participants in the control group was initially assumed to be around 60%, a recently concluded study [24] found that the proportion of participants recovering in the equivalent group was nearer to 20% (95% CI 12.9-30.3). Thus, the original power calculations were revised to reflect a reduced sample size of 360 patients randomised over a 27-month recruitment period.

As shown in Table 1, the revised power calculations provide adequate power for the primary analysis using the continuous outcome and, although there will inevitably be some reduction in power for the binary outcome, the ability to detect a 15% difference with 80% power remains.

**Table 1 T1:** Sample Size Calculation

total N randomised	N for primary analysis	power for 60% vs. 73% (OR = 1.80) ^1^	power for 20% vs. 33% (OR = 1.97) ^2^	detectable difference with 80% power ^3^	power to detect 3 BDI point difference
360	306	63%	69%	15%	82%

^1 ^based on original sample size

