## Discussion

This study has been designed to address the limitations highlighted in previous research on the subject of physical activity as a treatment for depression. All participants are recruited directly from within the primary care setting, thereby avoiding any undue influence from incentivisation and allowing the results to inform clinical practice. The study uses a remote randomisation system to protect concealment of allocation and proposes that the primary comparative analyses be conducted on an ITT basis in accordance with the CONSORT guidelines [20].

A two-arm design, with 180 participants per group should provide sufficient power to detect a meaningful difference in outcome. There will also be important supplementary CACE analyses to estimate efficiency in the presence of non-compliance with the intervention. All participants will be followed-up for a 12-month period, in order to consider the impact of the intervention in both the immediate and longer term. Finally, the intervention has been specifically developed to extend the scope of existing successful interventions and has robust theoretical underpinnings.

Physical activity, if found to be effective, could be an important alternative or adjunct treatment for depression, particularly for those who prefer non-pharmacological interventions. Currently, however, little is known about the mechanisms that might mediate any therapeutic effects of physical activity on depression. There are a number of hypothesised biological and psychosocial mechanisms but it is likely that an effective physical activity intervention would rely on multiple mechanisms. TREAD aims to evaluate, in general terms, whether physical activity can be an effective treatment for depression within primary care. Future research might identify which particular mechanisms, and any interactions between them, are most effective, as well as determining the optimum type, intensity and duration of physical activity required to produce a therapeutic effect.

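### The only clustering level the article names is general practice; clustering by facilitator, which exists in the intervention arm alone and does not cancel between arms, is not mentioned, so the primary CI and stated power may be optimistic

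*Protocol article*

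**What the plan says.** - **Allocation** (Randomisation procedure): "Eligible and consenting patients were individually randomised at the end of their baseline assessment". Antidepressant use is the stratifier. CIS-R severity, centre and activity level are minimised. Neither practice nor facilitator is a factor.
- **Delivery** (Intervention): "participants in the intervention arm of the study are offered the support of a Physical Activity Facilitator (PAF) over an 8-month period". The section speaks of PAFs in the plural but gives neither their number nor their caseloads. It describes tailored support, and also a manual, study-specific training and ongoing supervision.
- **Primary analysis** (Statistical Analysis): linear and logistic regression, with baseline BDI and the allocation factors as covariates.
- **Clustering** (Statistical Analysis): "The extent and impact on the results of clustering by general practice will also be investigated". No other level is named.
- **Power** (Sample size justification, Table 1): 360 randomised, 306 analysed and 82% power for 3 BDI points. No ICC or design effect appears.

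**The concern.** With individual randomisation, the patients of one practice can fall in either arm. Whatever they share through the practice then enters both arm means and mostly drops out of the difference. Correlation within practices therefore does little harm to the standard error of the treatment effect.

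Facilitators are different. Patients supported by the same facilitator may share that person's effect, and the control arm has no counterpart. Differences between facilitators therefore add variance to the intervention mean and to the contrast. Ordinary regression treats these patients as independent and does not count that variance.

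The article thus commits to examining the level that matters less for this comparison and does not mention the one that matters more. Practice is not a safe stand-in, because nothing in the article ties one facilitator to one practice. At stake are the coverage of the primary 95% CI and the realism of a power figure that stands only just above 80%.

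**Working it through.** **Inputs from the article**
- Two-sided alpha of 5%: "With 90% power and 5% two-sided alpha, 291 recruited patients would be required for each treatment group".
- 360 randomised: "the original power calculations were revised to reflect a reduced sample size of 360 patients randomised over a 27-month recruitment period". The Discussion confirms 180 per group.
- Attrition: the section works by "allowing for a maximum attrition rate of 15" per cent, so 360 × 0.85 = 306, or n = 153 per arm.
- SD 9: previous studies "have estimated a standard deviation of about 9 points".
- Target difference 3 points, stated power 82% (Table 1).

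**Inputs assumed, because the article gives none:** number of facilitators K, equal caseloads m = 153/K, and the ICC.

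**Step 1: reproduce the stated power.** SE₀ = 9 × √(2/153) = 1.029. Power = Φ(3/1.029 − 1.96) = 83.0% (82.8% with the noncentral t), against 82% stated. The binary figures also reproduce under independence, with a continuity correction:
- 291 per arm for 60% vs 73% at 90% power;
- at 153 per arm, 63.0% for 60% vs 73%, 68.9% for 20% vs 33%, and 80.6% for 20% vs 35%.

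The published calculations therefore contain no appreciable design effect.

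**Step 2: add clustering in the intervention arm only.**
- DE = 1 + (m − 1) × ICC
- Var(difference) = 81/153 + 81 × DE/153
- SE ratio = √((1 + DE)/2)
- Power = Φ(3/SE − 1.96)
- Type I error of the unadjusted test = 2 × (1 − Φ(1.96/SE ratio))

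Example with K = 4: m = 38.25. At ICC 0.01, DE = 1 + 37.25 × 0.01 = 1.37. The SE ratio is √(2.37/2) = 1.089, SE = 1.121, and power = Φ(3/1.121 − 1.96) = 76.3%.

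| PAFs | ICC | SE ratio | CI half-width | Power, 3 points | Type I error* |
|---|---|---|---|---|---|
| any | 0 | 1.000 | 2.02 | 83.0% | 5.0% |
| 4 | 0.01 | 1.089 | 2.20 | 76.3% | 7.2% |
| 4 | 0.02 | 1.172 | 2.36 | 70.1% | 9.4% |
| 4 | 0.05 | 1.390 | 2.80 | 55.5% | 15.8% |
| 10 | 0.01 | 1.035 | 2.09 | 80.4% | 5.8% |
| 10 | 0.02 | 1.069 | 2.16 | 77.8% | 6.7% |
| 10 | 0.05 | 1.165 | 2.35 | 70.6% | 9.3% |

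*Applies only if the average effect is zero while facilitators truly differ. All rows place every analysed intervention patient in a facilitator cluster.

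**Step 3: relax two assumptions.**
- *Uptake.* If 70% engage (assumed), K = 4 and ICC = 0.02, the cluster size is 0.7 × 153/4 = 26.8. Then DE = 1 + 0.7 × 25.8 × 0.02 = 1.36, the SE ratio is 1.087, power is 76.5% and type I error 7.1%.
- *Baseline adjustment.* Take a baseline correlation of 0.3 to 0.5 (assumed), K = 10 and the PAF variance at ICC 0.02 (0.02 × 81 = 1.62). Then Var = 2 × 81 × (1 − r²)/153 + 1.62 × 14.3/153, and power is 81% to 87%. Without the facilitator term the same adjustment gives 86% to 92%. Adjustment raises the level, but the loss of about 5 points remains.

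**The case against.** **The article is a condensation.** Its clustering sentence does not say that practice is the only level, and the full protocol and analysis plan are not shown. A reader might infer that facilitator effects will be ignored. The article does not support that; it supports only that they are not mentioned in it. The point survives because the article does more than stay silent: it selects a clustering level, and its power figures assume independence.

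**The size rests on assumptions.** That each facilitator sees many patients is plausible but stated nowhere. The manual, training and supervision are there to limit differences between facilitators. With 10 facilitators and an ICC of 0.01 the effect is slight. All of this stands.

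**The type I figures need an unusual null.** If support does nothing, facilitators do not differ through it and the test keeps its 5% level. An ICC of 0.05 implies a between-facilitator SD of √(0.05 × 81) = 2.0 points, so the 15.8% requires some facilitators to help and others to harm, averaging exactly zero. This stands, and those figures should not lead the argument.

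**The target of inference is a choice.** For the facilitators actually used, the ordinary standard error is defensible. But the Discussion wants results that inform practice, which implies other facilitators too. This favours a sensitivity analysis over replacing the primary model.

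**Conclusion.** The point holds in limited form. Facilitator clustering acts in one arm, is not mentioned in the article, and is absent from a power figure that reproduces under independence. If facilitators differ, the primary CI is too narrow and the Discussion's claim that "A two-arm design, with 180 participants per group should provide sufficient power to detect a meaningful difference in outcome" has less margin than it appears.

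The size is conditional. For ICCs of 0.01 to 0.05 with full uptake and equal caseloads, the SE ratio is 1.089 to 1.390 with 4 facilitators and 1.035 to 1.165 with 10. Incomplete uptake or a low ICC makes it smaller, and at an ICC of 0 it vanishes.

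A reader might go further and conclude that the primary analysis is invalid, or that the trial's true power is nearer half than 82%. The article supports neither, because it gives no number of facilitators, caseload or ICC. This is a worthwhile addition to the analysis, not a fault that overturns it.

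**What to change.** Keep the primary model and extend the clustering sentence in Statistical Analysis, along these lines:

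> As a sensitivity analysis beside the primary result, 4-month BDI will be refitted in a partially nested mixed model with a facilitator random effect in the intervention arm only, arm-specific residual variances and small-sample degrees of freedom. The number of facilitators, the facilitator ICC and the resulting CI will be reported. If facilitators are too few to estimate the ICC, the CI will be shown at fixed ICCs from 0 to 0.05.

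In Sample size justification and Table 1, state that the 82% assumes no clustering by facilitator.

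The cost is one extra model and no new patients or visits. It needs a record of which facilitator supported which patient, which the trial should already hold (an assumption). By the article's timetable, data collection ends in November 2010, so the model can be specified before analysis. The drawbacks are an imprecise ICC and, with very few facilitators, a CI that could be considerably wider. With 4, the between-facilitator variance rests on about 3 degrees of freedom, where the t quantile is 3.18 rather than 1.96. The contrast itself has somewhat more, because the control arm adds its own variance estimate. The fixed-ICC display shows the consequences of assumed values, not evidence from the trial, and should be labelled so.
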